#### Statistical methods

Qualitative variables, expressed as percentages, will be used for the descriptive analysis. The number of missing data will be recorded to check for dependence on study variables and to describe the individuals lost to follow-up during the study. Quantitative data will be described by means or medians, standard deviation, minimum and maximum values. Individual trajectories may also be plotted graphically.

For the primary endpoint analysis, we will use mixed models with latent classes to identify different digital phenotypes. The use of mixed models will make it possible to analyze repeat data for the population, and to determine an average profile or trajectory for the whole population. The choice of shape for this trajectory will be determined by testing (linear, quadratic, cubic or spline shape). The optimal number of classes will be determined a posteriori*,* based on a set of statistical and clinical criteria. The most widely used statistical criterion is the "Bayesian information criterion" (BIC), for which the likelihood of the model decreases with increasing complexity. The BIC, has been shown to outperform other, less strict criteria in simulations. The number of trajectories will also be determined on the basis of clinical interpretation (e.g. whether it is worthwhile retaining classes with very few members).

For the secondary endpoint analysis, the variables will be described, by trajectory, once the classes have been defined. We will compare means (Student's *t*-test), or categorical variables (chi^2^ tests). We will also perform multinomial logistic regression analyses with univariate and multivariate models, to determine the probability of belonging to a given class relative to the corresponding reference class. Time series forecasting will be used to predict events from a series of previous observations. This will make it possible to predict physiological changes in the participant based on her care trajectory and a series of observations of her physiological state, a potentially valuable indicator of the patient’s response to neoadjuvant treatment.

No imputation procedure will be required for missing data as we will use a maximum likelihood approach. Such approaches are robust to noninformative missing data, and a joint model will be used to take informative missing data into account, if necessary.

In terms of the development of algorithms and prediction models, we will:i) Compare the clinical data to a historical Institut Curie database containing data for patients receiving neoadjuvant treatment for BC collected between 2002 and 2011,ii) Compare the characteristics of our population with those of worldwide users of Withings Steel HR activity trackers of the same age and with a similar BMI. However, we will have no access to the medical histories of the other users,iii) Develop models for predicting treatment efficacy and toxicity. We will use the clinical data (personal information, pathological variables and treatment-related variables) and digital phenotype of the BC patient. Treatment toxicity will be evaluated with questionnaires based on the CTCAE criteria. Chemotherapy efficacy will be assessed by evaluating pathological complete response rates and determining the number of nodes sampled after NAC. We will train the model on 150 patients and validate it on the remaining 100 patients.iv) Develop models for predicting fatigue and changes in quality of life during treatment. We aim to develop a statistical model for detecting correlations between treatment-related variables (e.g. drugs taken, number of cycles and their dates) and periods of fatigue or deterioration of quality of life characterized by abnormal changes in physical activity. A training/validation strategy similar to that described in (iii) will be used.We will start by constructing the classification tool, which we will then validate before performing comparative studies based on the resulting classification.

Statistical analyses will be performed with R software.

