**Methods:**

NeoFit is a prospective, national, multicenter, single-arm open-label study. It will include 300 women below the age of 45 years treated with neoadjuvant chemotherapy for BC. Participants will be asked to wear a Withing Steel HR activity tracker round the clock for 12 months. The principal assessments will be performed at baseline, at the end of neoadjuvant chemotherapy and at 12 months. We will evaluate clinical parameters, such as toxicity and the efficacy of chemotherapy, together with quality of life, fatigue, and parameters relating to lifestyle and physical activity. The women will complete REDCap form questionnaires via a secure internet link.

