Digital health involves the collection of large amounts of data with various devices, including activity trackers and mobile phones [28]. Activity trackers can be used to evaluate the number of steps taken each day, the distance covered, energy expenditure, heart rate and the quality and duration of sleep [29]. Digital phenotyping is defined as the use of data from personal digital devices, including smartphones in particular, for instantaneous quantification of the human phenotype at individual level in situ [30]. This approach provides longitudinal data concerning the everyday activities of patients in a continuous and ecological manner. The combination of digital phenotyping data, clinical data and patient-reported outcomes can be used to identify patterns of behavior in patients; these patterns can then be used as the basis for the optimization of patient care through precision, predictive and personalized medicine [30–34].

The single-arm NeoFit trial will be an interventional single-arm study with the primary objective of describing and identifying digital profiles (physical activity, sleep and heart rate) in young BC patients (below 45 years of age) on NAC. Its secondary objectives will be: 1) to compare the digital profiles of participants according to clinical and sociodemographic variables, 2) to analyze the effects of digital profiles on tumor response, immune infiltrate, treatment toxicity, surgical complications, quality of life and fatigue, 3) to develop models for predicting chemotherapy response, toxicity, fatigue and changes in quality of life during treatment.

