### Evaluations

#### Modes of evaluation

All participants will attend three study consultations when attending the participating hospital center for their regular oncology consultation: an initial inclusion assessment (before the first day of neoadjuvant chemotherapy), a second assessment at the end of neoadjuvant chemotherapy, and a third assessment 12 months after inclusion (M12).

The activity tracker will collect information continuously via the Withings Health Mate application. At the end of the study, participants will be allowed to keep the activity tracker, with a transfer of the corresponding account to their own name.

Patient-reported outcomes will be evaluated by the answers provided on the questionnaires completed by all participants at the various time points. Patients will be able to assess the questionnaires directly via the REDCap Internet link of the NeoFit study, with a computer, smartphone or computer tablet. Each time that a new questionnaire requiring completion is posted online, the participants will be notified by e-mail and asked to complete it. If they encounter any problems completing the questionnaire, they will be able to contact the clinical research assistant to ask for help.

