#### Quality of life

Quality of life will be assessed with the European Organisation for Research and Treatment of Cancer Quality of Life Questionnaire (EORTC QLQ-C30) version 3, which was validated in 2000 [35]. This multidimensional questionnaire has been validated for use with cancer patients. It contains 30 items assessing five functional domains (physical, role, emotional, cognitive, and social), one overall quality-of-life domain, three symptom domains (pain, fatigue and nausea), and six individual items (dyspnea, insomnia, anorexia, diarrhea, constipation, and financial impact). Responses will be on a Likert scale ranging from "not at all" to "very much" and from "very poor" to "excellent" for the overall quality-of-life questions only. Scores will be standardized on a scale of 0 to 100. Higher scores will correspond to better functioning, a better overall quality of life and more symptoms. Mean completion time for this questionnaire has been estimated at 10 min.

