#### Fatigue

Fatigue will be evaluated with the EORTC QLQ-FA12 version 1 module, which was validated for cancer-related fatigue in 2017 [36]. EORTC QLQ-FA12 contains 12 items assessing the physical, cognitive, and emotional domains of cancer-related fatigue. Participants will complete a four-point Likert-scale questionnaire, with responses ranging from "not at all" to "very much".

Scores will be standardized on a scale of 0 to 100, with higher scores suggesting a greater degree of fatigue. This questionnaire has an estimated completion time of five minutes.

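### For the effects of digital profiles on quality of life and fatigue, the only test named for means is Student's t-test, which makes no use of baseline scores or of the repeated measurements

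*Protocol article*

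**What the plan says.** The second secondary objective, at the end of the Background, is "to analyze the effects of digital profiles on tumor response, immune infiltrate, treatment toxicity, surgical complications, quality of life and fatigue".

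Quality of life (QLQ-C30) and fatigue (QLQ-FA12) are each scored from 0 to 100. They come from "questionnaires completed by all participants at the various time points". The abstract gives the timing: "The principal assessments will be performed at baseline, at the end of neoadjuvant chemotherapy and at 12 months".

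Under Statistical methods, the repeated-measures model is assigned to forming the classes: "For the primary endpoint analysis, we will use mixed models with latent classes to identify different digital phenotypes". For the secondary endpoints, variables are described by trajectory once the classes exist, and then: "We will compare means (Student's *t*-test), or categorical variables (chi^2^ tests"). The section adds multinomial logistic regressions, univariate and multivariate, with class membership as the outcome; their covariates are not listed. It also plans time series forecasting. Separately, the paragraph on algorithms and prediction models plans to predict fatigue and change in quality of life from treatment-related variables.

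**The concern.** Comparing means between classes compares different women, so the t-test is a two-sample test with one value per woman. It has no place for her baseline score unless that score is built into the value compared, and the text does not say that it is.

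The classes are formed from the women's own activity, sleep and heart rate. A woman who is already more tired, or has poorer quality of life, before chemotherapy can be expected to move less and to fall into a low-activity class. Part of any class difference at the end of chemotherapy or at month 12 may then have been present at the start. If follow-up means are compared, that earlier difference can be reported as an effect of the profile, which is what the objective asks about.

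This does not depend on how many classes are found or how surely women are assigned to them. It arises even with two perfectly known classes.

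**Working it through.** **Inputs from the article.** 300 women are included, with 10% loss assumed: 300 × 0.90 = 270, consistent with the stated minimum of 250 evaluable. I use 250. The article's only other computed figure, the precision of about 8% for 150 subjects, reproduces as 2 × √(0.5 × 0.5 / 150) = 0.082 with p = 0.5 assumed. It has no bearing here.

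**Assumptions, not in the article.** Two known classes of 125; unit SD; baseline gap d in SD units; baseline/follow-up correlation ρ of 0.3 to 0.7; two-sided 5% level.

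**Standard error of a difference in follow-up means.** √(1/125 + 1/125) = 0.1265 SD.

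**Null A: no class effect given baseline.** The expected follow-up difference is ρ × d. With d = 0.3 and ρ = 0.5 it is 0.15 SD, and 0.15 / 0.1265 = 1.186. The rejection rate is Φ(1.186 − 1.96) + Φ(−1.186 − 1.96) ≈ 0.220. For a change score the expected difference has size (1 − ρ)d and the SD is √(2(1 − ρ)).

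| d | ρ | t-test, follow-up | t-test, change |
|---|---|---|---|
| 0.3 | 0.3 | 11% | 29% |
| 0.3 | 0.5 | 22% | 22% |
| 0.3 | 0.7 | 38% | 15% |
| 0.5 | 0.3 | 22% | 65% |
| 0.5 | 0.5 | 51% | 51% |
| 0.5 | 0.7 | 79% | 33% |

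Simulation with 4,000 runs agrees. At d = 0.3, ρ = 0.5 the follow-up t-test rejects 22.9% and ANCOVA on baseline 5.3%. At d = 0.5, ρ = 0.5 the figures are 50.6% and 5.0%. With d = 0 both stay near 5% (4.9% and 5.7%). With a 175/75 split, d = 0.3 and ρ = 0.5, the follow-up t-test rejects 19%.

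**Null B: equal mean change in both classes.** The follow-up difference is now the whole gap d.

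- Follow-up t-test, d = 0.3: 0.3 / 0.1265 = 2.372, giving 66% whatever ρ is.
- ANCOVA, d = 0.3, ρ = 0.5: the expected coefficient is (1 − ρ)d = 0.15. Its standard error is √(1 − 0.25) × 0.1265 × √(1 + 0.09/4) = 0.1108. The ratio is 1.354, giving 27% (26% to 28% in simulation).
- t-test on change scores: about 5%.
- At d = 0.5, ρ = 0.5: about 98% for the follow-up t-test and 59% to 60% for ANCOVA.

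Using the baseline score therefore beats the follow-up t-test under either null, but which use of it holds 5% depends on the null.

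**Does another named method supply the adjustment?** The latent-class mixed model forms the classes. The treatment-variable prediction models do not compare classes. A multinomial model could do it: with baseline and follow-up scores both entered, the follow-up coefficient tests the same conditional association as ANCOVA. In two-class simulations under Null A it rejected 4.8% to 5.6%. The article does not say that both scores will be entered.

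**The case against.** The strongest reply is that the sentence is generic. It does not say which variable, which visit or which kind of score is compared, and it also serves the first secondary objective, where unadjusted t-tests and chi-squared tests by clinical and sociodemographic variables are ordinary. A reader might infer that the plan discards each woman's baseline score. The text does not say so; that reading rests on its silence. Likewise, that baseline gaps will be reported as effects is a risk, not a stated rule.

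A second reply is that covariates and score definitions are usually left to the full protocol or analysis plan. This is fair as far as missing detail goes. The visit schedule for the two questionnaires is also not spelled out in their own sections; it is inferred from the abstract and the evaluation section. But the article does name a method for means, and that method cannot by itself answer the objective. Resolving the ambiguity does not help: a t-test of baseline scores shows no effect, a t-test of follow-up scores carries the gap over, and a t-test of change scores is right only if equal mean change is the intended null.

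A third reply is that the t-test is not the only secondary method. This stands. A reader might infer that the multinomial models are useless here because class is their outcome; that is wrong, as shown above. The obstacle is only that their covariates are not stated.

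Finally, the study is exploratory with no power target, so the gain in precision from adjustment carries little weight.

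**Conclusion.** The point holds in this limited form: for quality of life and fatigue, the only test named for class means provides for neither baseline nor repeated measurement, and so cannot by itself support a statement about effects of profiles.

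For a 0.3 SD baseline gap and correlation 0.5, a follow-up t-test would reject about 22% of the time with no class effect given baseline, and about 66% with equal mean change. These are illustrations. The gap, the correlation and the two equal classes are assumed, and the article gives none of them.

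A reader might also conclude that baseline adjustment keeps the error near 5% in all circumstances. It does so only under the conditional null. In non-randomised classes the choice between ANCOVA and change scores depends on the estimand, and neither removes other confounding. Because the work is exploratory and secondary, this is a worthwhile correction and no threat to the primary aim.

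**What to change.** In Statistical methods, for QLQ-C30, FA12 and any other score also measured at baseline, replace the t-test with a linear mixed model for repeated measures on the end-of-chemotherapy and month-12 scores. Use class, visit and class-by-visit as terms, with the baseline score as covariate for the conditional difference. In addition:

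- State the target estimand.
- Report the class difference in change from baseline as a sensitivity analysis.
- Describe baseline scores by class separately, as characteristics.
- Word the results as associations.
- Keep unadjusted tests for variables measured once.

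The cost is a few sentences. No further patients or data are needed, provided the baseline questionnaires are collected as the abstract indicates. The downside is small: women without a baseline questionnaire need baseline and follow-up modelled jointly, which fits the maximum likelihood approach the section already adopts. Residual confounding between classes will remain.

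### Student's t-test does not fit a comparison across three or more latent classes, and comparing after classification shrinks class differences when assignment is imperfect

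*Protocol article*

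**What the plan says.** All references are to the protocol article.

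- **Number of classes** (Statistical methods): "The optimal number of classes will be determined a posteriori", using BIC and clinical interpretation.
- **Comparison by class** (same section, secondary endpoint analysis): "the variables will be described, by trajectory, once the classes have been defined". The tests are then named: "We will compare means (Student's *t*-test), or categorical variables (chi^2^ tests".
- **Regression** (next sentence): "We will also perform multinomial logistic regression analyses with univariate and multivariate models", whose purpose is "to determine the probability of belonging to a given class relative to the corresponding reference class". Class membership is therefore the dependent variable.
- **Order of work** (end of the section): the classification tool is built first, "which we will then validate before performing comparative studies based on the resulting classification".
- **Objectives** (end of Background): the first secondary objective is "to compare the digital profiles of participants according to clinical and sociodemographic variables"; the second is "to analyze the effects of digital profiles on tumor response, immune infiltrate, treatment toxicity, surgical complications, quality of life and fatigue".
- **Prediction models** (numbered list in Statistical methods): item iii predicts efficacy, including pathological complete response (pCR), and toxicity from clinical data together with the digital phenotype. Item iv relates periods of fatigue or worse quality of life to treatment variables such as drugs and cycles.

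**The concern.** Three things in the secondary analysis sit badly together.

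First, the only test named for means handles two groups, while the plan leaves the number of groups open and names a regression that is needed only for three or more. An analyst following the text with three or more classes must either depart from it or run a set of pairwise t-tests, for which no multiplicity control is stated.

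Second, latent class is estimated, not observed. If each woman is placed in one class and the classes are then compared, women placed wrongly mix the groups and pull their means together. Real differences between phenotypes then look smaller than they are, and confidence intervals miss the true value too often.

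Third, objective 2 treats the profile as the exposure and the clinical endpoints as outcomes. The regression in the secondary analysis runs the other way. That suits objective 1 but is a poor match for objective 2.

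**Working it through.** **Inputs.** The plan gives no figure for these comparisons. Its one computed precision, about 8% at 150 subjects, reproduces as 2 × √(0.5 × 0.5 / 150) = 0.082 (p = 0.5 assumed) but does not bear on this point. The usable input is the evaluable number, at least 250 of 300; with 10% lost, 300 × 0.9 = 270, which is consistent. The 5% two-sided level, number of classes, class sizes, class separation and effect sizes below are assumptions.

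**1. Pairwise t-tests.** With K classes there are m = K(K − 1)/2 pairs. If the tests were independent, the chance of at least one false difference would be 1 − 0.95^m. They share data, so the true chance is lower and was simulated with no true difference, equal classes and about 250 women. Two independent simulations (4,000 and 3,000 runs) gave:

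| K | Pairs | Independence formula | Simulated, pairwise t | Simulated, one-way ANOVA |
|---|---|---|---|---|
| 2 | 1 | 0.050 | 0.056 | 0.056 |
| 3 | 3 | 0.143 | 0.123 and 0.129 | 0.052 |
| 4 | 6 | 0.265 | 0.207 and 0.191 | 0.043 |
| 5 | 10 | 0.401 | 0.287 and 0.300 | 0.057 |

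(The K = 2 row and the ANOVA column come from the 3,000-run simulation only.) These chances are per continuous variable. The chi-square test extends to any number of classes, so categorical variables are unaffected.

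**2. Classify, then compare.** Each of 250 women was assigned to her most likely class, and two adjacent classes with a true difference of 0.5 SD were compared (2,000 runs, class parameters taken as known). Attenuation is 1 − estimate/0.5.

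| Classes | Correctly assigned | Mean estimate (SD) | Attenuation | 95% CI coverage |
|---|---|---|---|---|
| 2 | 77% | 0.271 | 46% | 58% |
| 2 | 84% | 0.344 | 31% | 79% |
| 2 | 93% | 0.431 | 14% | 91% |
| 2 | 98% | 0.474 | 5% | 94% |
| 3 | 70% | 0.376 | 25% | 88% |
| 3 | 79% | 0.420 | 16% | 92% |
| 3 | 91% | 0.470 | 6% | 95% |
| 3 | 97% | 0.492 | 2% | 95% |

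The model standard error matched the empirical one (for example 0.130 against 0.132), so coverage was lost through attenuation.

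The error pattern matters too. With three equal classes, accuracy a and errors split equally between the other two classes, differences shrink by the factor a − (1 − a)/2: 0.85 at a = 0.9, 0.70 at 0.8 and 0.55 at 0.7, or 15%, 30% and 45% attenuation. As an illustration, assumed pCR rates of 25/40/55% at a = 0.8 would appear as 29.5/40/50.5%; for the first class, 0.8 × 25 + 0.1 × 40 + 0.1 × 55 = 29.5.

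**3. Objective 2 against the named models.**

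| Outcome in objective 2 | By-class test (unadjusted) | Model naming the phenotype as predictor |
|---|---|---|
| Tumour response | yes | yes, item iii |
| Toxicity | yes | yes, item iii |
| Immune infiltrate | yes | none named |
| Surgical complications | yes | none named |
| Quality of life, fatigue | yes | not named; item iv uses treatment variables |

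**The case against.** The strongest reply is that the study is exploratory, its main objective is descriptive, and this is a secondary analysis reported in a condensed article. Two classes remain possible, in which case the t-test is valid. The text specifies neither pairwise testing nor a significance level, and the multinomial model already offers a multi-class comparison against a reference class. All of this is fair, and it limits the weight of the point. It does not rescue the named test, which is stated text and does not fit the case the same paragraph anticipates.

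On class uncertainty, the phrases about timing do not say outright that assigned class is treated as known, and handling of posterior probabilities may be set out in an analysis plan that is not shown. This part therefore rests on the stated order of work only. Validating the tool first does not remove assignment error from later comparisons.

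A reader might infer that objective 2 goes unanswered, or that no adjusted effect on response will be estimated. The documents do not support that. Item iii places efficacy and toxicity as outcomes with the phenotype beside clinical predictors, and the by-class tests give an unadjusted answer for every outcome. Moreover, if a binary outcome such as pCR enters the multivariate multinomial model, its odds ratio with class measures essentially the same conditional association. That argument does not carry over to a mean difference in a quality-of-life or fatigue score.

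A reader might also expect standard errors that are too small. The simulation shows no such effect, although it took class parameters as known and so does not measure the error from estimating them.

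**Conclusion.** The point holds in a limited form.

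- **Test for means:** firm. Student's t-test does not fit three or more classes. The false-difference chances of about 12–13%, 19–21% and 29–30% for 3, 4 and 5 classes apply if the test is run as unadjusted pairwise comparisons at 5%, which is an assumption about how the text would be carried out.
- **Classify, then compare:** the direction is clear; the size is not. Attenuation is negligible when nearly all women are correctly assigned and substantial at 70–80%. It is larger with two classes, or with errors spread evenly across classes, than in the three-class simulation. Class separation is not given, so no single percentage, including the 30% in the pCR illustration, should be read as a forecast.
- **Objective 2:** a narrow gap. No adjusted model with class as exposure is named for immune infiltrate, surgical complications, quality of life or fatigue.

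This is a weakness in a secondary, exploratory analysis. It should be corrected before analysis but does not threaten the primary objective.

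**What to change.** 1. Replace Student's t-test with an overall test across classes (one-way ANOVA or Kruskal-Wallis), followed by pairwise contrasts with multiplicity control. Keep chi-square for categorical variables.
2. State that class uncertainty is carried into the comparisons, by a bias-adjusted three-step method or by repeated draws from the posterior class probabilities, and report classification accuracy with the results.
3. Keep the multinomial model for objective 1. For objective 2, add regressions with class as exposure for immune infiltrate, surgical complications, quality of life and fatigue, adjusted for prespecified pre-treatment covariates. Tumour subtype is an obvious one, since the eligibility criteria admit every subtype. Say whether the item iii models are also meant to give the adjusted class effect on efficacy and toxicity.

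The cost is a change of wording and modest programming in R, with no new data. Confidence intervals will be somewhat wider.

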## Methods

### Study design

The NeoFit study is a prospective, national, multicenter, single-arm, open-label study promoted by the Institut Curie (Paris, France) (Fig. 1). It will enroll 300 participants from two comprehensive cancer care centers in France, beginning in September 2021 during a one-year period.

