### Statistical analysis

#### Sample size

 As the main objective of the study is descriptive, there is no need to define a minimum number of subjects. For model validation, we will divide our population into two groups: i) a training sample (*n* = 150) and ii) a validation sample (*n* = 100). The accuracy of the model for 150 subjects will therefore be about 8%.$$CI=2\times \surd \frac{p\times q}{n}$$

We hypothesize that 10% of the participants may be lost to follow-up. In the context of this study, that would mean not completing the questionnaires despite reminders, or not wearing the activity trackers. The inclusion of 300 participants is therefore expected to result in the collection of at least 250 completed questionnaires and 250 activity tracker datasets.

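### A single 150/100 split is valid but inefficient for the prediction models; resampling over all evaluable women would give tighter performance estimates with no added patients

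*Protocol article*

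**What the plan says.** The Sample size section states: "For model validation, we will divide our population into two groups", with 150 women for training and 100 for validation. It adds: "The accuracy of the model for 150 subjects will therefore be about 8" per cent, from the formula 2 × √(p×q/n), without giving p. On numbers, it says "We hypothesize that 10% of the participants may be lost to follow-up" and "The inclusion of 300 participants is therefore expected to result in the collection of at least 250 completed questionnaires and 250 activity tracker datasets".

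Item (iii) of the Statistical methods section covers the models for efficacy and toxicity: "We will train the model on 150 patients and validate it on the remaining 100 patients". Item (iv), on fatigue and quality of life, adds: "A training/validation strategy similar to that described in (iii) will be used". The list closes with: "We will start by constructing the classification tool, which we will then validate before performing comparative studies based on the resulting classification".

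Neither section mentions an allocation rule, repeated splitting, cross-validation, bootstrap or a final refit on all women. On the source of the women, Study design says: "It will enroll 300 participants from two comprehensive cancer care centers in France". The digital phenotype is one of the predictors in item (iii). It comes from latent-class mixed models whose number of classes is settled afterwards, partly by BIC and partly by clinical interpretation.

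**The concern.** Developing prediction models is the third secondary objective, so how well they perform is a result of the study. With about 250 women, one split costs twice. The model is fitted on 60% of the data (150/250), and its performance is then read from the other 40% in one partition, so the estimate depends on which women fall on which side. The only precision figure in the protocol uses the training sample size, although performance will be measured on the 100 validation women. A reader would therefore expect a tighter result than the plan can deliver.

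**Working it through.** **Inputs.** From the protocol: 300 enrolled; at least 250 evaluable; 150 training and 100 validation; half-width formula 2 × √(p×q/n); pCR in 20-60% of patients (Background). Assumed, because not given: p = 0.5 (range 0.2-0.8 shown), the AUC, and the number and strength of predictors.

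**1. Reproduce the stated figure.** At p = 0.5 and n = 150: 2 × √(0.25/150) = 0.0816, or about 8%. It reproduces, as a half-width on the training sample.

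**2. The same formula on other sample sizes.**

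| n | role | p = 0.5 | p = 0.2 or 0.8 |
|---|---|---|---|
| 100 | planned validation | 10.0 points | 8.0 points |
| 150 | planned training | 8.2 points | 6.5 points |
| 250 | all evaluable | 6.3 points | 5.1 points |
| 270 | 300 × 0.9 | 6.1 points | 4.9 points |

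From 100 to 250 the half-width falls by 1 − 6.3/10.0 = 37%. The value at 250 is a binomial approximation to the precision of a resampled estimate, not an exact one.

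**3. Cross-check on the AUC scale.** The Hanley-McNeil variance is [A(1−A) + (n1−1)(Q1−A²) + (n0−1)(Q2−A²)]/(n1·n0), with Q1 = A/(2−A) and Q2 = 2A²/(1+A). Take A = 0.70, so Q1 = 0.538 and Q2 = 0.576.
- pCR 20%, n = 100 (n1 = 20, n0 = 80): SE 0.071, 95% half-width 0.138. At n = 250 the half-width is 0.087.
- pCR 60%, n = 100: half-width 0.102. At n = 250: 0.064.

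At 20% pCR the planned interval is therefore about 0.56 to 0.84.

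**4. Events for model fitting.** At 20% pCR, 150 women give 30 events and 250 give 50. At 40% the counts are 60 and 100.

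**5. Simulation under assumed settings.** Logistic model, 250 women, 10 or 20 predictors (half with a true effect), event rate 20% or 40%, 200 replicates per setting. The 150/100 split was compared with bootstrap optimism correction and repeated 10-fold cross-validation on all 250.

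| AUC, by predictors / event rate | true AUC, 150 → 250 | RMSE split | RMSE bootstrap | RMSE CV | bias split / bootstrap / CV |
|---|---|---|---|---|---|
| 10 / 20% | 0.696 → 0.712 | 0.067 | 0.045 | 0.053 | −0.002 / 0.008 / −0.015 |
| 10 / 40% | 0.706 → 0.719 | 0.053 | 0.038 | 0.040 | 0.004 / 0.007 / −0.007 |
| 20 / 20% | 0.664 → 0.688 | 0.066 | 0.050 | 0.049 | 0.006 / 0.028 / −0.011 |
| 20 / 40% | 0.672 → 0.693 | 0.055 | 0.044 | 0.042 | 0.008 / 0.021 / −0.004 |

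The RMSE ratios to the split are 0.67-0.79 for the AUC, an error 21-33% smaller. For classification accuracy they are 0.63-0.76, or 24-37% smaller. Over both measures the reduction in mean squared error is a factor of 1.6 (1/0.79²) to 2.5 (1/0.63²). The gain in the model itself is 0.013 to 0.024 in AUC and 0.8 to 1.8 points in accuracy.

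**The case against.** **The split is a legitimate method.** Its bias in the simulation is at most 0.008, while bootstrap correction stayed optimistic by 0.02-0.03 in AUC with 20 predictors. Item (iii) lists personal, pathological, treatment and digital variables, so many predictors are plausible. This stands. It rules out calling the plan invalid, and it favours repeated cross-validation over the simple bootstrap when predictors are many.

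**The gains depend on assumptions.** The number of predictors, their strength and the event rate are not in the protocol. The simulated model had no latent-class step, so the gain is not shown for the full pipeline. This stands too; the figures indicate the order of size only.

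**Clinical judgement cannot be resampled.** Because the number of classes is partly a clinical decision, an untouched hold-out suits the plan better unless that decision becomes a fixed rule. This is correct, and it is a real cost of the change.

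**These are secondary aims.** The main objective is descriptive and the study exploratory, and a fuller document might add resampling. That limits the weight of the point. But the article fixes the 150/100 scheme in two places, so it can be judged as written.

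**A reader might infer that the validation women contaminate the predictor,** because the latent-class analysis is described for the whole population. The text does not establish this. That wording explains what a mixed model estimates, and the closing sentence on building and then validating the tool fits derivation in the training women only. The risk is conditional on a choice the article leaves open. Likewise, the protocol never presents the split as external validation, and it neither states nor excludes a split by centre or period.

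**Conclusion.** The point holds as an efficiency improvement, not as an error. At p = 0.5, validated accuracy would carry a half-width of 10.0 points on the planned 100 women (8.0-10.0 over p = 0.2-0.8), not the stated figure of about 8%. Using all 250 brings it to roughly 6.3 points. Under the assumed simulation settings, resampling lowers the error of the performance estimate by about a fifth to a third for the AUC, and by up to 37% for accuracy.

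A reader might infer that resampling would yield a clearly better model. The figures do not support that: the true AUC rises by only about 0.01 to 0.02. The main benefit is a more precise statement of how well the model performs. With either method this remains internal validation, since no separation by centre or period is stated.

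**What to change.** - Develop each model in items (iii) and (iv) on all evaluable women (at least 250). A 10% loss from 300 would leave 270, about 20 more than the 150/100 scheme assigns.
- Report discrimination and calibration from repeated cross-validation, preferred when predictors are many, or from bootstrap optimism correction.
- Repeat every data-driven step inside each resample: trajectory shape, number and derivation of latent classes, class assignment, predictor selection and model fitting. For this purpose, replace clinical judgement on the number of classes with a prespecified automatic rule, for example BIC plus a minimum class size.
- If a hold-out is kept, derive the classes in the training women only and quote precision at n = 100.
- Describe the result as internal validation.

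The cost is computing time, a change to the analysis plan, the need to fix the class-selection rule in advance, and the loss of a single untouched hold-out set. No patients, visits or data are added.
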